### Randomisation

Children will be matched in pairs according to age (12 month age bands), gender, side of hemiplegia, and level of functional ability based on MUUL scores at screening. Once matching has been achieved and baseline assessments completed, children will be randomised within pairs from concealed envelopes opened by non-study personnel. Treatment allocation will be recorded on a piece of folded paper inside each envelope in random order (computer generated). The randomisation process will involve allocating a number "1" or "2' to each member of the pair which will be written on the paper inside the envelope. As each pair is entered, they will be allocated the next consecutive envelope, which will be opened by the non-study personnel who will read and record the treatment allocation from the paper inside the envelope. Study personnel will be informed of group allocation.

A matched pairs design is the design of choice as it minimises the likelihood of group differences at baseline that has often been present in UL rehabilitation studies[21,29]. In order to maximise group coherence, camps will be conducted in two age bands (two camps each of CIMT and BIM training for children 5-10 years and one camp each of CIMT and BIM training for children 11-16 years).

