### Sample size

According to CONSORT guidelines the primary basis for sample size calculation is adequate power for the comparison between the functional effects of CIMT and BIM training at 3 weeks post intervention. Based on data from a previous study[33], a mean difference of 7 percentage points was proposed or 10% of the anticipated control group mean at baseline on the Melbourne Assessment of Unilateral Upper Limb Function[34] as the minimum difference that is likely to have substantial clinical importance. Our pilot data in a study of UL training with and without intramuscular BoNT-A injections yielded standard deviation of changes of 7.6 and 9.6 units in the two groups. Based on a t-test comparison of changes using a SD of 9 units for both groups, significance (alpha) level of 0.05, and 80% power, we require 26 participants in each group (total sample of 52).

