### Study treatments

Each intervention will be delivered in groups of 9 to 13 children for 6 hours per day for 2 weeks (10 days) in a day camp model. The total dosage of intervention will be 60 hours. After baseline assessment and randomisation children will attend either the two week BIM training camp or immediately following, a two week CIMT camp. One week of the camp will be during school term and one during school holidays. To optimize children's engagement in the intervention, day camps will be run at a community sporting facility and will employ a circus theme with circus activities provided by professional trainers and an additional day-excursion to an adventure "low ropes" course. Consistent with self determination theory[35] to maximize motivation the key elements of competence, autonomy and relatedness will be incorporated. Competence will be achieved through scaffolding of activities to optimise success, autonomy by allowing choice, and relatedness through the sharing of the experience with others of similar abilities.

Both groups will receive the same dosage and content of intervention, delivered in the same environment. Participants in the CIMT group will wear a tailor made glove on their unimpaired limb while attending the day camp, which will only be removed for toileting. Table 1 summarises the components of each intervention. The tasks for each camp will be designed to enable either maximal bimanual use of the hands for the designated tasks and modified for the CIMT camp to perform the same tasks in a unimanual approach with constraint on the unimpaired hand.

**Table 1 T1:** Summary of intervention content

Session (and Activities)	Allocated Time	CIMT: Type of involved hand use	BIM training: Type of involved hand use

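### Treatment is given in three group camps per arm, but the sample size and between-group tests assume independent children, so the stated 80% power holds only without within-camp correlation

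*Protocol article*

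**What the plan says.** - **Unit of randomisation** (Randomisation): "children will be randomised within pairs from concealed envelopes opened by non-study personnel". Pairs are matched on age, gender, side of hemiplegia and screening score on the Melbourne assessment (MUUL).
- **Unit of delivery** (Randomisation, Study treatments): the camps are split by age, with "two camps each of CIMT and BIM training for children 5-10 years and one camp each of CIMT and BIM training" in the older band. That is three camps per arm and six in all. "Each intervention will be delivered in groups of 9 to 13 children", for 60 hours in total.
- **Sample size**: the target effect is 7 points on the MUUL, a two-sample t-test on changes with SD 9 is the method, and the result is stated as "we require 26 participants in each group (total sample of 52").
- **Analyses**: between-group differences at each of the three follow-ups are tested, as an initial step, with independent t-tests or the Wilcoxon rank sum test.

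The sample size and the tests include no camp term, intra-camp correlation or design effect, and no allowance for the pairing. The article fixes both methods itself, so the point does not depend on an analysis plan that is not shown.

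**The concern.** Children in one camp share peers, volunteer staff and calendar weeks, and a programme that is adjusted after each session. The Study treatments section also makes relatedness, gained by sharing the experience with other children, a deliberate ingredient. Changes in MUUL may therefore be correlated within a camp.

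With three camps per arm, one unusually good or poor camp is about a third of an arm, and such variation does not average out. Matching balances age band between arms. It cannot absorb camp-to-camp variation within an arm, because the two members of a pair always attend different camps. Two things are at stake: whether 52 children deliver the stated power, and whether the reported standard error reflects the real uncertainty.

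**Working it through.** **Inputs.** From the Sample size section: difference 7, SD of change 9, alpha 0.05 (taken as two-sided), 26 per arm. From Randomisation: 3 camps per arm, so m = 26/3 = 8.67 children per camp. The ICC and the within-pair correlation r are not in the document. Both are assumptions, shown over a range.

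**1. The plan's own figure.** n per arm = 2 × 9² × (1.96 + 0.84)² / 7² ≈ 25.9, so 26. With SE = 9 × √(2/26) = 2.50, power = Φ(7/2.50 − 1.96) = 80.1%. The exact t calculation gives 78.5%. A one-sided test would need 21. The stated 26 is therefore a two-sided calculation for independent children, with no design effect.

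**2. Power with camp correlation.** Design effect DE = 1 + (m − 1) × ICC. Power = Φ(7 / (2.50 × √DE) − 1.96). This is the same normal approximation as in step 1, with no credit for matching.

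| Assumed ICC | DE | Effective n per arm (26/DE) | Power for 7 points |
|---|---|---|---|
| 0 | 1.00 | 26 | 80% |
| 0.01 | 1.08 | 24 | 77% |
| 0.05 | 1.38 | 19 | 66% |
| 0.10 | 1.77 | 15 | 56% |

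**3. Error bars of the planned unpaired test.** That test ignores both camp and pair. Relative to the variance it assumes, the true variance of the difference is about 1 + (m − 1) × ICC − r. It is too liberal only when (m − 1) × ICC exceeds r, that is when r is below 7.67 × ICC:
- ICC 0.01: r below 0.08
- ICC 0.05: r below 0.38
- ICC 0.10: r below 0.77

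Type I error is about 2 × (1 − Φ(1.96 / √(DE − r))). At ICCs of 0.01, 0.05 and 0.10:
- r = 0: 5.9%, 9.6% and 14.0%
- r = 0.4: 1.7%, 4.8% and 9.4%

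**4. Error bars of a paired test without a camp term.** Its assumed variance is already reduced by the factor 1 − r, so the ratio of true to assumed variance is (DE − r) / (1 − r). At r = 0.1 this is 0.977/0.9 = 1.09, 1.283/0.9 = 1.43 and 1.667/0.9 = 1.85. The type I error is about 6%, 10% and 15%. A simulation with camps of 9, 9 and 8 children per arm gave 6.0%, 10.0% and 14.8%. Pairing removes the offset in step 3 and leaves the camp problem.

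**5. Cost of a camp-level test.** Six camps in two arms leave 6 − 2 = 4 degrees of freedom. A camp-level t-test for 7 points has about 56% power even at ICC 0.

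**6. Camp size.** Three camps of at least 9 need 3 × 9 = 27 per arm, against the stated 26.

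**The case against.** **The ICC may be close to zero.** The Therapy protocols and delivery section has the same three occupational therapists and one physiotherapist lead all groups, with one staff member to two children and activities graded daily for the participants. Dosage, content and environment are meant to be common to both arms, and one masked rater is to assess the MUUL. Nothing in the text supports any particular ICC. This stands, and it is why the range starts at zero and no single power loss is claimed.

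**Matching may offset clustering.** A reader might infer that the planned test must exceed 5% type I error. The documents do not support that: step 3 shows it depends on r, which is not given and could be substantial because pairs are matched on the outcome instrument itself. This also stands. However, the offset is two unmodelled features happening to cancel, and it disappears once the pairs are analysed as pairs.

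**Part of an apparent power loss can come from switching formula.** Setting exact-t powers under clustering against the stated 80% would mix methods, since the exact t is already at 78.5% with no clustering. The table in step 2 uses one method throughout.

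**The named tests are only an initial step.** A camp sensitivity analysis could sit in a document not shown. That limits any complaint about a missing analysis. It does not change the sample size calculation, which is complete in the article and assumes independence.

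**Conclusion.** The point holds as a limit on the power statement. On the plan's own calculation, 80% requires zero within-camp correlation. Under assumed ICCs of 0.01 to 0.10 it falls to between 77% and 56% before any gain from matching. That gain cannot be sized because r is unknown.

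The stronger reading, that the planned error bars are too narrow and type I error is inflated, is conditional on r lying below the thresholds in step 3. It applies more directly to a paired analysis without a camp term. Nor do the documents show that outcomes will cluster by camp, only that the design permits it and the plan does not allow for it. The mismatch of one child per arm in camp size is minor and does not bear on clustering.

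**What to change.** 1. In the Sample size section, state that the calculation assumes independence within camps, and give the power over an ICC range such as 0 to 0.10 beside the 80%.
2. Make the primary MUUL analysis respect the pairs.
3. Beside it, report a prespecified sensitivity analysis with a camp random effect (six camps) and small-sample degrees of freedom, and a leave-one-camp-out check. Neither should be a condition for concluding superiority: a 4-degree-of-freedom test as the deciding analysis would cut power to about 56% even with no clustering.
4. Reconcile 26 per arm with three camps of at least 9.

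The cost is wording, a less favourable stated power, and a wide sensitivity interval, because camp variance is poorly estimated from 4 degrees of freedom. Enlarging the existing camps would help little. Recovering the power lost to clustering would need more camps.

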### Study treatments

Each intervention will be delivered in groups of 9 to 13 children for 6 hours per day for 2 weeks (10 days) in a day camp model. The total dosage of intervention will be 60 hours. After baseline assessment and randomisation children will attend either the two week BIM training camp or immediately following, a two week CIMT camp. One week of the camp will be during school term and one during school holidays. To optimize children's engagement in the intervention, day camps will be run at a community sporting facility and will employ a circus theme with circus activities provided by professional trainers and an additional day-excursion to an adventure "low ropes" course. Consistent with self determination theory[35] to maximize motivation the key elements of competence, autonomy and relatedness will be incorporated. Competence will be achieved through scaffolding of activities to optimise success, autonomy by allowing choice, and relatedness through the sharing of the experience with others of similar abilities.

Both groups will receive the same dosage and content of intervention, delivered in the same environment. Participants in the CIMT group will wear a tailor made glove on their unimpaired limb while attending the day camp, which will only be removed for toileting. Table 1 summarises the components of each intervention. The tasks for each camp will be designed to enable either maximal bimanual use of the hands for the designated tasks and modified for the CIMT camp to perform the same tasks in a unimanual approach with constraint on the unimpaired hand.

**Table 1 T1:** Summary of intervention content

Session (and Activities)	Allocated Time	CIMT: Type of involved hand use	BIM training: Type of involved hand use
**Fine motor activity stations**			
a) Games	1 hour	Reach, precision grasp, power grasp, tool use, controlled placement and release, finger isolation, in-hand manipulation, wrist extension, supination	Stabilisation, symmetric and asymmetric bilateral movements, precision grasp, controlled placement and release, finger isolation, in-hand manipulation, wrist extension, supination
b) Functional tasks			
c) Cooking			
d) Art and crafts			
**Circus Workshop**			
a) Warm up and stretch	2 hours	Active stretching whole body	Active stretching whole body
b) Ribbons		Grasp, shoulder external and internal rotation, adduction, horizontal abduction, flexion, elbow and wrist extension, supination	Grasp, shoulder external rotation, adduction, horizontal abduction, elbow and wrist extension. Symmetric movements.
c) Devil Sticks		Grasp, shoulder adduction and flexion, elbow and wrist extension	Grasp, symmetric shoulder flexion, elbow extension, wrist extension. Asymmetric shoulder adduction.
d) Hoops		Grasp, shoulder adduction and flexion, elbow extension, supination and wrist extension.	Grasp, shoulder adduction and flexion, elbow and wrist extension. Asymmetric movements
e) Spinning plates			Grasp, shoulder adduction and flexion, elbow extension, supination and wrist extension, finger isolation, asymmetric bilateral movement
f) Acrobalance		Strength, dynamic and static balance	Strength, dynamic and static balance
g) Aerials		Power grasp, upper body strength.	Power grasp, upper body strength & symmetry.
**Mealtimes**			
a) Preparation	1.5 hours	Grasp and transportation, precision grasp, tool use, elbow flexion, extension, supination, wrist extension, radial deviation	Stabilisation, grasp, tool use (knife and fork), asymmetric bilateral movements
b) Eating			
c) Cleanup			
**Games**			
a) Parachute		Grasp, shoulder flexion, extension, adduction, elbow and wrist extension, supination, throw and catch	Symmetric and asymmetric movements, stabilisation, grasp, shoulder flexion, extension, adduction, elbow and wrist extension, supination
b) Sports			
**Debriefing**	0.5 hour	Group discussion about day	Group discussion about day

Children will return to their regular therapy programs at the completion of the 2-week program. Documentation of concurrent therapy programs (ongoing, additional therapy or interventions, change in spasticity, medications or lower limb interventions) will be recorded at each follow up assessment as these would not be able to be controlled over a 12 month period.

### Outcome measures and procedures

A number of classification measurements will be used to describe the sample at the level of brain structure, brain reorganisation, manual abilities, severity of impairment (body structure) and gross motor function. This study will be the first to our knowledge to comprehensively measure and compare the impact of two models of UL intervention across all domains of the ICF[4].

#### 1. Classification of the sample

The participants entered into the study that meet the inclusion criteria will be classified according to:

##### a) Manual Abilities Classification System (MACS)

The MACS classifies the child's ability to handle objects in daily activities on one of 5 levels[36]. The MACs has reported construct validity, and excellent inter-rater reliability (ICC 0.97 between therapists and 0.96 between therapists and parents)[36]. It is expected that all children in the sample will be MACS level I (able to handle objects easily and successfully) or level II (able to handle most objects but with somewhat reduced quality and/or speed of achievement so that alternate ways of performance might be used).

##### b) Gross Motor Function Classification System (GMFCS)

The GMFCS classifies the child's ability to carry out self initiated movements related to sitting and walking across 5 levels[37]. The GMFCS has strong construct validity with the Gross Motor Function Measure (r = 0.91)[38] and good inter observer reliability between professionals and between professionals and parents[39,40]. In this sample of children with congenital hemiplegia it is expected that most children will be GMFCS level I or II.

##### c) Zancolli Scale

The Zancolli Scale[41] classifies severity of forearm alignment by measuring the contribution of spasticity and muscle length in the wrist and finger flexors in active wrist and finger extension. The Zancolli scale was developed to classify impairment and alignment of the hemiplegic hand before and after surgery. Three levels range from I (minimal flexion spasticity, complete extension of fingers with wrist in neutral position or less than twenty degrees of flexion) to III (severe flexion spasticity, no extension of fingers even with maximal wrist flexion). It is expected that participants will have either a level I or II Zancolli score.

##### d) House Functional Classification Scale

The House Functional Classification Scale[42] was originally developed to evaluate hand function following surgery. It consists of nine grades ranging from 0 (does not use) to 8 (full spontaneous use). The House scale will be used to rate functional use of the impaired UL. Both the Zancolli Scale and House Functional Classification Scale have been found useful in describing hand function in a population based survey of children with CP[43].

#### 2. Primary and Secondary Outcome Measures

The primary outcome measure of interest is UL activity performance for unimanual capacity using the Melbourne Unilateral Upper Limb Assessment at 26 weeks follow up. Secondary measures include measures across all domains of the International Classification of Functioning, Disability and Health (ICF).

Measures of body structure will include both the positive features of the upper motor neurone syndrome (muscle spasticity, length) and the negative features (weakness, dexterity and sensation). Positive features will be assessed in the impaired (hemiplegic UL) while negative features will be compared between limbs (to account for any unintended effects of wearing the constraint on the unimpaired hand in the CIMT group).

Measures of activity will assess unimanual capacity in the impaired limb (using the MUUL), bimanual performance between the upper limbs (using the Assisting Hand Assessment) and the achievement of individualised outcomes (with the Canadian Occupational Performance Measure). Participation will be assessed at home, in school and community life using both child and parent proxy response. Environmental barriers and facilitators to participation will be evaluated. In addition to these measures, the broad domains of quality of life will be assessed.

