### Analyses

All assessment forms will be developed using scannable Teleforms (Teleform, 2005). Forms will be entered, scanned and visually checked by staff trained in use of the software. Data will be transferred electronically into Microsoft Access 1997. Analyses will be on an intention-to-treat basis using STATA 10. Data from each outcome measure will be summarised for each treatment group and descriptive statistics (frequencies, means, medians, 95% confidence intervals) calculated dependent on data distribution. We anticipate that groups will be similar on baseline measures due to the matched pairs design. Initially between group differences will be evaluated at the three follow-up assessment points using independent t-tests or Wilcoxon rank sum test. Within group changes between baseline and the follow-up assessments for continuous variables will be evaluated using paired t-tests or Wilcoxon matched-pairs sign rank test. A significance level of 0.05 will be used.

For the TMS data Student's paired t-test will be used for analysis of the difference between pre and each post intervention (3 and 26 weeks) mean MT and MEP ratios. This will be performed in each group for the impaired side and the unimpaired side.

To determine the intra-rater reliability of our trained occupational therapist rater on the MUUL, intraclass correlation coefficients will be calculated (3.1) with 95% confidence intervals from total MUUL percentage scores[101]. The standard error of measurement (SEM = SD × √(1-ICC)) and the smallest detectible difference (SDD = SEM × 1.96 × √2) will be calculated[102].

Post hoc analyses will be undertaken to investigate clinical characteristics of children who have a greater response to either intervention.

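### The 80% power is stated for the 3-week comparison, but the primary outcome is declared at 26 weeks, so power for the declared primary test is not established

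*Protocol article*

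**What the plan says.** Four parts of the protocol article bear on the point.

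- **2. Primary and Secondary Outcome Measures** makes unimanual capacity the primary outcome, "using the Melbourne Unilateral Upper Limb Assessment at 26 weeks follow up". This is the only place where a visit is attached to the term primary outcome. The later description of the Melbourne assessment (MUUL) again calls it primary but gives no visit.
- **Sample size** takes as its primary basis "adequate power for the comparison between the functional effects of CIMT and BIM training at 3 weeks post intervention". The target is "a mean difference of 7 percentage points was proposed or 10% of the anticipated control group mean at baseline". The calculation is "Based on a t-test comparison of changes using a SD of 9 units for both groups", with "significance (alpha) level of 0.05, and 80% power", giving 26 per group and 52 in total. The pilot data behind the SD "yielded standard deviation of changes of 7.6 and 9.6 units in the two groups".
- **Methods/Design** (opening section) describes the 26- and 52-week visits as follow-up to see whether effects are retained.
- **Analyses** compares the groups at all three follow-up visits without singling one out, and adds: "A significance level of 0.05 will be used".

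The Abstract gives the recruitment target as 52 children in 26 matched pairs, which is exactly the calculated number.

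**The concern.** A trial's power statement should belong to the test that decides the trial. Here the decisive test is placed at 26 weeks and the power statement at 3 weeks. Two things follow.

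1. A reader cannot tell what power the declared primary test has. The document itself gives reasons why 26 weeks may differ from 3. The specific aims allow that effects may be short lived. Under Study treatments, children go back to their regular therapy after the camp, and concurrent therapy is recorded because it cannot be controlled. Loss to follow-up also has more time to accumulate.
2. The sample size and the retention wording lean towards 3 weeks, the outcome section names 26 weeks, and the analysis section treats the three visits alike. A report could therefore give prominence to whichever of the two visits looked better and cite the protocol for it.

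**Working it through.** **Inputs from the Sample size section:** difference δ = 7 percentage points; SD of change σ = 9 in both groups; α = 0.05; power 80%; equal groups. Sidedness is not stated, but two-sided reproduces the plan's figure and one-sided does not (it gives 21 per group by the normal formula).

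**Step 1: reproduce the plan's figure.** Normal approximation, per group:

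n = 2(1.960 + 0.842)² σ²/δ² = 2 × 7.849 × 81/49 = 25.95, rounded up to 26.

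Power at n = 26: Φ(δ/(σ√(2/26)) − 1.960) = Φ(2.804 − 1.960) = 0.801.

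The exact two-sided t-test (50 degrees of freedom, critical value 2.009, noncentrality 2.804) gives power 0.785 at 26 per group and needs 26.94, so 27, for 80%. The stated 26 is the normal-approximation answer. It is correct for the inputs given, and the gap of about 1.5 points is not the issue.

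**Step 2: what must hold for that figure to apply at 26 weeks.** The formula uses δ, σ and the number analysed.

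- δ is presented as a minimum clinically important difference with no visit attached, so it can reasonably be kept at 7.
- σ rests on pilot SDs of 7.6 and 9.6, also given without a visit. Nothing says that 9 is the SD of change at 26 weeks.
- The number analysed is 26 per group only if nobody is lost.

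**Step 3: power at δ = 7 when σ or the number analysed varies** (exact two-sided t-test, α = 0.05, noncentrality 7/(σ√(2/n))).

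| SD of change | n per group | Power |
|---|---|---|
| 7.6 (lower pilot SD) | 26 | 90% |
| 8.66 (pooled pilot SD, equal pilot groups assumed) | 26 | 82% |
| 9 (plan) | 26 | 78.5% |
| 9.6 (upper pilot SD) | 26 | 73% |
| 9, assumed 5% loss | 24.7 | 76% |
| 9, assumed 10% loss | 23.4 | 74% |
| 9, assumed 20% loss | 20.8 | 69% |

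The pooled SD is √((7.6² + 9.6²)/2) = √74.96 = 8.66. The loss percentages are assumptions, because the document gives none.

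**Step 4: cost of leaving two visits open.** If success could be claimed at 3 or at 26 weeks, each tested two-sided at 0.05, the chance of at least one false positive is 1 − P(|Z₁| < 1.96 and |Z₂| < 1.96). With an assumed correlation between the two test statistics of 0.5, 0.7 and 0.9 this is 0.091, 0.083 and 0.070. Under independence it would be 1 − 0.95² = 0.0975.

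**The case against.** The best defence is that only one section attaches the term primary outcome to a visit. The Sample size section speaks of the basis for a calculation, and that is not a second declaration of the endpoint. On this reading 26 weeks is primary, and testing other visits at 0.05 does not inflate the error of a named primary test. This stands. A reader might infer that the protocol declares two rival primary endpoints, and it does not. The 7% to 9% figure is therefore conditional on someone using the 3-week visit as an alternative route to success. A similar figure for three visits has no basis, because 52 weeks is nowhere given primary status.

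A reader might also infer that the trial is underpowered at 26 weeks, for instance because an effect that fades to 5 points would give about 50% power. The documents do not support this either. Five points lies below the plan's own minimum important difference, and a trial sized on such a difference is not expected to keep 80% power beneath it. Nor does the SD have to be larger at 26 weeks: at the lower pilot SD, power is 90%.

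Finally, the 7-point difference and the pilot SDs carry no visit, so it would go too far to call them 3-week values. Only the comparison being powered is placed at 3 weeks.

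What the defence does not remove is the mismatch. Condensation into a journal article does not explain it, because both visits are stated outright, and an unseen analysis plan could not agree with both sections without adding the missing link.

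**Conclusion.** The point holds as an internal inconsistency: the visit for which the trial is powered is not the visit at which its primary outcome is declared, and no section bridges the two. The stated 80% is not established for the declared primary test. That is different from showing that the power is below 80%. At the plan's 7-point difference, power at 26 weeks could plausibly lie on either side: 90% to 73% across the pilot SDs with nobody lost, and 74% at SD 9 with 10% lost. These figures assume a two-sided t-test on changes, equal groups, and pilot SDs that remain relevant at 26 weeks; the loss rate is assumed. The type I error of about 7% to 9% applies only if either visit may be claimed as the primary result, and rests on an assumed correlation of 0.9 to 0.5. It needs fixing because it settles which single test decides the trial.

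**What to change.** Name one primary time point and use it consistently in Sample size, in Primary and Secondary Outcome Measures, and in Analyses. As the text stands, 26 weeks is the declared one.

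- In Sample size, restate the power that 52 children achieve at that visit for the 7-point difference, giving the SD of change and the retention assumed there, preferably over a short range.
- In Analyses, identify the between-group MUUL test at that visit as primary and label the tests at the other visits secondary.
- If 3 weeks is what was intended, change the outcome section instead and leave 26 and 52 weeks as retention assessments.

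The cost is a few sentences in three sections. The downside is that the stated power may become less favourable: allowing for any loss at SD 9 brings it below the quoted 80%. Whether to recruit more children is a separate decision, to be taken once the assumptions for the chosen visit are stated.
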